To the authors’ knowledge, the TRACE Programme is the first MI-based telehealth intervention used in combination with personalised coping skills training for the management of addictive eating in adults. The aim of the current study is to determine the efficacy of a telehealth intervention (active intervention) to reduce symptoms of addictive eating in adults, relative to passive intervention and control (no intervention) groups. It is hypothesised that both the active and passive intervention groups will achieve a reduction in addictive eating symptoms relative to the control group. Potential moderators (eg, participant sociodemographics) and mediators (eg, physical activity, diet and sleep) of intervention efficacy will also be evaluated.

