### Sample size

The sample size for the study was calculated based on data from the feasibility study,^24^ given the absence of other intervention studies. Through guidance with statisticians, a large effect size was chosen and needed to enable the possibility of a clinically meaningful result. A clinically meaningful difference in symptoms of addictive eating was selected as a decrease of two symptoms, given this would correspond to a change in severity classification on the YFAS 2.0 tool. To detect a mean two-unit difference (SD=2.2) in the YFAS symptoms between the active intervention group and the passive intervention group or control group and using a standardised effect size of d=0.91, a sample size of 32 individuals per group (total sample size n=96) is required to detect this change with a power of 0.90 and a type 1 error rate set at 0.025 to account for multiple testing. However, allowing for a 30% dropout rate from the pilot, a sample size of 46 individuals per group (total sample size n=138) would be required. Therefore, a total sample size of 150 individuals, with 50 per group, was chosen to remain conservative.

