### Statistical analysis plan

Data analysis will be conducted by a researcher blinded to the intervention conditions. Descriptive statistics of sample characteristics will be presented. For the primary YFAS outcome, a linear mixed model (LMM) will be based on a model with main effects for group (active intervention, passive intervention, control) and time (treated as categorical at levels baseline, 3 and 6 months), and the group-by-time interaction. An unstructured residual covariance structure will be used to allow for correlation between the repeated measurements for a subject. The primary outcome effect will be reported as the difference between means at baseline and 3 months, with a 95% CI for the difference. Mental health condition and BMI will be examined for possible moderating effects on the effect size, and if so, adjustment for them will be carried out. Secondary descriptive analysis will be carried out to identify whether specific symptoms were predominantly associated with reductions in YFAS score.

A secondary outcome will be a categorical variable, clinically significant change from baseline to 3 months, where significant requires a reduction of two or more symptoms in the YFAS. This will be analysed using logistic regression with group being the only factor. Additional secondary outcomes will include dietary outcomes (average daily energy intake, proportion of total energy intake contributed by core food and non-core food intake, macronutrient intake, micronutrient intake and overall diet quality) and mental health status (depression, anxiety and stress scores). These will also be analysed using LMMs as per the approach above. All available data will be used with no imputation of missing values at 3 and 6 months; however, baseline scores will be kept. The participants will be analysed according to their allocated randomisation group consistent with an intention-to-treat analysis. Statistical significance will be set at 0.05.

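### The sample size uses 0.025 per comparison for multiplicity, but the analysis section states 0.05 with a 95% CI and leaves passive versus control without a declared status

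*Protocol article*

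**What the plan says.** Three parts of the protocol article bear on the primary comparisons.

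- **Introduction, last paragraph.** The aim is the efficacy of the active programme "relative to passive intervention and control (no intervention) groups", which means active versus passive and active versus control. The hypothesis is that "both the active and passive intervention groups will achieve a reduction in addictive eating symptoms relative to the control group", which means active versus control and passive versus control.
- **Sample size.** The calculation is for a difference "between the active intervention group and the passive intervention group or control group", with "a type 1 error rate set at 0.025 to account for multiple testing". Its inputs are a two-symptom difference, SD 2.2, d=0.91 and power 0.90. They give 32 per group, 46 after 30% dropout, and 50 per group chosen.
- **Statistical analysis plan.** The primary outcome is analysed with a mixed model with group, time and their interaction. The effect is reported "with a 95% CI for the difference", and the section ends with "Statistical significance will be set at 0.05". It gives no division of alpha across contrasts, no testing order and no overall test that must be passed first.

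**The concern.** The design adjusts for multiple comparisons and says so. The section that governs the analysis states an unadjusted level and does not mention the adjustment. A primary p-value between 0.025 and 0.05 would be significant under one section and not under the other, and nothing in the article settles which applies. That leaves the main efficacy decision open to choice once results are known.

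The set of primary contrasts is also unsettled. The aim and the sample size share one pair and the hypothesis uses another. Passive versus control appears only in the hypothesis, so no share of alpha was planned for it.

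**Working it through.** **1. Reproduce the planned sample size.** Inputs from the Sample size section: difference 2, SD 2.2, power 0.90, alpha 0.025. Effect size d = 2/2.2 = 0.909. The article does not state whether the test is one- or two-sided, so both were tried with the two-sample t-test (noncentral t):

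| Alpha | Sides | n per group |
|---|---|---|
| 0.025 | two | 32 |
| 0.025 | one | 27 |
| 0.05 | two | 27 |
| 0.05/3 = 0.0167 | two | 35 |

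Of the two readings of 0.025, only the two-sided one gives the stated 32. Dropout: 32/0.70 = 45.7, so 46, also as stated. The arithmetic is correct, and 0.025 is best read as 0.05/2, a two-sided Bonferroni share for two contrasts.

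**2. Family-wise error.** With equal allocation (Randomisation and blinding section), any two pairwise contrasts share an arm and their test statistics have correlation 0.5 in absolute value. The figures below come from simulating three equal arms (3 million draws), with each contrast tested two-sided on its own:

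| Level per contrast | Two contrasts | All three |
|---|---|---|
| 0.05 | 9.0% | 12.2% |
| 0.025 | 4.6% | 6.4% |
| 0.0167 | 3.1% | 4.4% |

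As a cross-check, treating the contrasts as independent gives upper figures of 1 − 0.95² = 9.75% and 1 − 0.95³ = 14.3%. The values at 0.05 lie below these, as they should.

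**3. How far this depends on the null.** The table assumes that all three arms have the same mean. If they do not, at most one of the three pairwise nulls can be true, and testing each at 0.05 then gives a family-wise error of at most 5%.

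**4. Effect of a prior overall test.** If pairwise tests at 0.05 were made only after a significant overall three-arm test at 0.05, the simulated family-wise error with equal arms is 5.0%. The article specifies no such step.

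**5. Power under the planned enrolment.** Completers per arm: 50 × 0.70 = 35. With d = 0.909, two-sided power is 93.2% at 0.025 and 90.8% at 0.0167. The 35 per group needed at 0.0167 inflates to 35/0.70 = 50, exactly the number chosen. For passive versus control this assumes the same two-symptom difference, which the article states only for contrasts with the active arm.

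**6. Price in interval width.** Normal multipliers are 1.960 (95%), 2.241 (97.5%) and 2.394 (98.33%, that is 1 − 0.05/3). Ratios: 2.241/1.960 = 1.14 and 2.394/1.960 = 1.22.

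**The case against.** The strongest reply is that the two sections can be reconciled. The 0.05 can be read as the overall level that the Sample size section splits in two. The sentence is generic and closes a paragraph that is mostly about secondary outcomes, and it does not withdraw the adjustment. The 95% CI is attached literally to the difference between baseline and 3 months, and a reporting interval does not by itself fix the test level. Each statement of purpose also contains only two contrasts, which 0.025 would cover.

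Much of this stands, and it limits what can be claimed. A reader might infer that the trial is committed to twice its intended false-positive rate. The documents do not support that: the adjustment is not carried forward, but neither is it revoked, and 9.0% is a worst case with equal arms and separate tests. A reader might also take 12.2% as the trial's error rate. That figure needs the union of the contrasts in the aim and the hypothesis, and nothing in the article declares all three jointly primary. The remark under Limitations about both interventions proving effective discusses implications and is not a planned test.

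The reply does not remove the conflict. The section is headed as the statistical analysis plan and states a level and an interval, so this is not detail left to another document. Reading 0.05 as the overall level sits poorly with the 95% interval. It also leaves passive versus control unplaced, since three contrasts at 0.025 give 6.4%. One can argue that multi-arm trials need not always adjust, but this design chose to.

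**Conclusion.** The point holds as an unresolved conflict in the primary decision rule. The design level is 0.025 per comparison, two-sided by inference from n=32, while the analysis section states 0.05 with a 95% CI. If 0.05 is used for each contrast with no prior overall test, family-wise error with all arms equal is up to 9.0% for two contrasts instead of the 4.6% the design implies. It is 12.2% only if all three contrasts are treated as primary. If the arms are not all equal, it does not exceed 5%. Separately, passive versus control is hypothesised but not in the sized pair, so its status has to be declared. The sample size is not in question: using 0.05 would raise power (94.7% at 32 per group), so what is at risk is the type I error.

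**What to change.** State in the Statistical analysis plan section which 3-month between-arm contrasts form the primary family, and make the level and intervals match. Either of these is consistent with the design:

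- **Two primary contrasts.** Name the two, test each at two-sided 0.025 with 97.5% CIs, and label the third as secondary. If the sized pair is kept, passive versus control becomes secondary and the hypothesis in the Introduction should be reworded to match.
- **Three primary contrasts.** Control family-wise error at 0.05 with Holm, or with Bonferroni at 0.0167. Report CIs at the Bonferroni level (98.33%), which is also the simple choice alongside Holm.

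In both cases, state that the tests are two-sided and restrict "Statistical significance will be set at 0.05" to the secondary outcomes. Pairwise tests after a significant overall test would also control the error with three arms, but would have to be written in.

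The change is to wording only and needs no further participants. It should be recorded before the unblinded comparison, through the route for protocol modifications that the article describes. The cost is primary intervals about 14% wider (two contrasts) or 22% wider (three) than at 95%, with planned power still 93.2% or 90.8%.

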### Data management and monitoring

Online survey data will be managed using REDCap (Research Electronic Data Capture) electronic data capture tools^91 92^ hosted at the University of Newcastle. REDCap is a secure, web-based software platform designed to support data capture for research studies, providing (1) an intuitive interface for validated data capture; (2) audit trails for tracking data manipulation and export procedures; (3) automated export procedures for seamless data downloads to common statistical packages; and (4) procedures for data integration and interoperability with external sources.

All data captured from the study website will be encrypted and stored securely on the server. All other data collected will be entered into a password-protected central database, which is hosted on secure university-based servers, which comply with robust security standards for clinical data and are subject to daily backups and regular offsite backups. Only authorised members of the research team will have access to the database. Research staff handling study data are trained in procedures for handling sensitive information, accurate data entry, surveillance and intervention-specific data storage and data archive. Facilitators of the telehealth sessions are responsible for the electronic storage of study forms on the central database. All completed forms will be checked for completeness and accuracy, first by data collectors and later by a member of the research team responsible for data management. Throughout the study period (at 25% and 50% of required participants), approximately 5% of records will be randomly selected for data quality checks of accuracy and completeness by an independent reviewer.

A Data Safety Monitoring Board will not be established for this study as all elements of the intervention have been previously explored and used in interventions. To monitor for potential risks, the study coordinator managing the day-to-day conduct of the trial, and facilitators of the telehealth sessions, will report weekly to the chief investigator. Oversight concerning the overall conduct of the trial will be provided by our multidisciplinary research team. This will include regular meetings to review protocol adherence, participant retention rates and safety reports. For the entire study period, any adverse events, of any kind, that might be related to either the trial intervention or trial procedures will be logged in an adverse event log and reported to the Human Research Ethics Committee by the chief investigator. To maintain the welfare of participants, with their consent, relevant survey results from the GAD-7^60^ and PHQ-8^63^ will be sent to the participant’s nominated general practitioner/health professional if they score in the severe category for either anxiety (GAD-7 scores ≥16) or depression (PHQ-8 scores ≥20), if participants consent to this disclosure.

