### Randomisation and blinding

Following completion of baseline assessments, participants will be stratified into four groups by sex and mental health status (presence or absence, based on either depression scale PHQ-8 scores ≥15 or below 15, or anxiety scale GAD-7 scores ≥11 or below 11). Participants within each of these four groups will be randomised to one of the three study groups in equal ratios using permuted block randomisation, with block sizes of six. Randomisation will promote group balance on these variables shown to be important in past cross-sectional research (for example, 7 8 10 65). The randomisation sequence will be generated by an independent statistician and implemented by a designated study coordinator. The allocation list will be stored in a password-protected computer file and accessed only by the study coordinator.

Due to the telehealth nature of the active intervention, blinding of participants and dietitians to intervention group allocation in this study will not be possible. However, several strategies will be employed to reduce the risk of bias. First, participants will only be provided with partial information on the study hypotheses. Second, all communication between participants and research staff during the period of intervention (ie, scheduling concerns, questions regarding the intervention) will be done directly between participants and the ‘study coordinator’ or their respective ‘telehealth clinician’. Lastly, statistical analyses will be conducted by researchers who are blind to group allocation prior to analysis.

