### TRACE active intervention (group 1)

Participants will receive five standardised one-on-one telehealth/phone sessions with an Accredited Practising Dietitian, with training in behaviour change and eating disorders, over a 3-month period (ie, weeks 1, 2, 4, 8 and 12). Additionally, dietitians leading the intervention delivery will have extensive experience in private practice work and working with clients including those with disordered eating and those with mental health conditions. Sessions will range from 15 to 45 min. Telehealth sessions will be provided via the VSee platform (www.vsee.com). The active intervention uses personalised feedback, skill-building exercises and goal setting to help individuals reduce their symptoms of addictive eating and improve their dietary intake and relationship with food (see table 2 for overview of intervention sessions). The intervention is personalised based on an individual’s dominant trait/s associated with personality and risk of addictive behaviour (ie, the traits: depression proneness, anxiety proneness, sensation proneness and/or impulsivity proneness; measured via the Substance Use Risk Profile Scale,^37^ which the individual scores the most highly for) and addresses a range of factors that influence behaviour, both internal and external. Further, dominant trait/s associated with personality and risk of addictive behaviour are mapped to specific coping skill strategies, which are in turn incorporated into the goal-setting process. As part of session 1, the first 15 min of the consultation will be audio recorded to enable qualitative analysis of responses to two standardised questions regarding the elements of ‘control’ and ‘compulsion’ around the participant’s food intake. These two themes were previously identified, through thematic analysis of the feasibility study data,^66^ as having an influential relationship with addictive eating behaviours. On completion of the five telehealth sessions, participants will be invited to join a closed Facebook group from 3 months post-commencement of the intervention until the 6-month outcome survey measures are conducted. Joining the Facebook group is voluntary.

**Table 2 T2:** Overview of intervention sessions

Session	Session aims

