### TRACE passive intervention (group 2)

Participants will receive the intervention via self-guided approach, with access to the five-module workbook and website (as described above), but without the telehealth consults. The content of the workbook modules mirrors the content of the five telehealth sessions. In addition to the written materials provided, the workbook contains spaces for reflective activities, documenting goals and monitoring progress. Participants will be asked, on receipt of the workbook, to complete the workbook within a 3-month period. The proportion of the workbook completed by participants in the passive intervention arm will not be monitored. Following the 3-month self-guided learning period, participants will be invited to join the closed Facebook group as described above.

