### Control (group 3)

Participants will receive personalised dietary feedback on baseline surveys, provided by an automated report, generated from the Australian Eating Survey. This is consistent with standard dietary feedback from a dietitian. Participants in the control group will be offered access to the participant workbook and study website after the completion of the 6-month assessment.

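### The adverse-event log cannot support a between-arm statement about harm, and the eating-disorder risk that the protocol screens out has no stated by-arm harm summary although comparable data are scheduled in every arm

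*Protocol article*

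**What the plan says.** **Logging rule.** Under Data management and monitoring, "any adverse events, of any kind, that might be related to either the trial intervention or trial procedures will be logged", and the chief investigator reports these events to the ethics committee. For monitoring risks, the study coordinator and "facilitators of the telehealth sessions, will report weekly to the chief investigator". There is no data safety monitoring board.

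**Who knows allocation.** Under Randomisation and blinding, "blinding of participants and dietitians to intervention group allocation in this study will not be possible". The coordinator also knows the arm: "The allocation list will be stored in a password-protected computer file and accessed only by the study coordinator".

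**Contact by arm.** In the active arm, "Participants will receive five standardised one-on-one telehealth/phone sessions with an Accredited Practising Dietitian". The passive arm has the workbook and website "but without the telehealth consults". In the control arm, "Participants will receive personalised dietary feedback on baseline surveys, provided by an automated report".

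**Eating-disorder risk.** The eligibility sections exclude anyone reporting purging on the EDE-QS. They also exclude BMI below 18.5, to make recruitment of people with risky restrictive eating less likely. Table 1 schedules EDE-Q 6.0 at baseline, 3 and 6 months under mediators/moderators, and self-reported weight at screening, 3 and 6 months under sample characteristics. The Statistical analysis plan section uses BMI only as a possible moderator. Its secondary outcomes are a two-symptom YFAS reduction, dietary outcomes, and depression, anxiety and stress scores.

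**The concern.** Two features make the log's counts non-comparable between arms.

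- **Entry filter.** An event enters only if someone thinks it might be related, and both named reporters know the arm. The Introduction describes the comparison as "relative to passive intervention and control (no intervention) groups". The same event could therefore look related in the active arm and unrelated in the control arm. An event refused at entry cannot be recovered by later analysis.
- **Contact.** Facilitators, one of the two named reporting sources, meet only active-arm participants.

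The article commits to CONSORT reporting. If log counts were published by arm, a difference could reflect judgement or contact rather than harm, and a short list in the passive or control arm would not show that little happened there. Meanwhile the harm that the protocol itself guards against at entry is measured identically in every randomised arm but is given no descriptive harm role.

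**Working it through.** **1. Contact.** Session lengths in Table 2 give 45 + 45 + 30 + 30 + 20 = 170 scheduled minutes with a facilitator in the active arm. The passive and control arms have 0.

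**2. What unequal detection could do (illustration only).** The document gives no event or detection rates, so those below are assumptions. Take 50 per arm (Sample size section), the same true event rate in both arms, and independent binomial counts with p = rate × detection. The entries are the chance that the active log exceeds a low-contact arm's log:

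| Detection, active v other | rate 2% | rate 5% | rate 10% |
|---|---|---|---|
| 60% v 10% | 0.421 | 0.700 | 0.874 |
| 50% v 20% | 0.338 | 0.554 | 0.705 |
| 40% v 30% | 0.259 | 0.404 | 0.495 |
| 30% v 30% (no gap) | 0.201 | 0.316 | 0.378 |

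The excess over the no-gap row is large only if the gap is wide.

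At a true rate of 10% (50 × 0.10 = 5 expected cases), the chance of an empty log in a low-contact arm is (1 − 0.10 × detection)^50. This is 0.605, 0.364 and 0.218 at detection of 10%, 20% and 30%.

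**3. Does logging everything cure this?** Suppose the relatedness filter passes half of detected events equally in both arms. Removing it at a true rate of 10% is then the same as moving from the 5% column to the 10% column. The chance of a spurious active-arm excess rises: 0.700 to 0.874, 0.554 to 0.705, 0.404 to 0.495. Removing the filter takes away a judgement made with knowledge of the arm. It does not equalise detection.

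**4. What the scheduled survey data can deliver.** With the 30% dropout in the Sample size section, completers are 50 × 0.70 = 35 per arm.

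- Zero events: one-sided 95% upper bound = 1 − 0.05^(1/35) = 8.2%.
- 2 of 35 = 5.7%; exact (Clopper-Pearson) 95% CI 0.7% to 19.2%.
- 4 of 35 against 2 of 35: difference 5.7 points; Newcombe 95% CI −8.9 to 20.8.
- Between-arm difference in EDE-Q change, approximated by a change-score comparison: half-width = t(68) × √(2/35) × √(2(1 − ρ)) in SD units. With an assumed ρ = 0.5 this is 1.9955 × 0.2390 × 1.000 = 0.48 SD. With ρ = 0.7 it is 1.9955 × 0.2390 × 0.775 = 0.37 SD.

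These estimates are imprecise, but they come from the same instrument at the same times in each arm.

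**The case against.** The other side has a good case on several points.

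- **No log comparison is planned.** The log's one stated use is reporting to the ethics committee, and a log of possibly related events serves that. This stands: the log limits what may later be said, but no planned analysis is wrong.
- **The coordinator is not tied to one arm.** Randomisation and blinding routes participants' communication to the coordinator or their telehealth clinician, and every arm receives study emails and survey reminders. A reader might infer that the passive and control arms have no route to the log. The document does not support that. It supports only that scheduled facilitator contact is confined to one arm.
- **The filter is broad.** It covers trial procedures, which all arms undergo, and the Intervention and Cost analysis sections count control among the intervention arms. The article does not say who judges relatedness, or that the two named reporters are the only sources. A reader might infer that control events would be systematically rejected. That is possible but not stated.
- **Comparable safety information exists.** With consent, severe GAD-7 or PHQ-8 scores go to the participant's nominated health professional, with no restriction by arm. Depression, anxiety and stress scores are also modelled by group. This stands for mood and anxiety, but does not reach purging, restriction or weight.
- **Placing EDE-Q as a mediator or moderator does not forbid describing it by arm.** True, but no such description is stated, and the purpose given is to examine efficacy.

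**Conclusion.** The point holds as a minor one. The article fixes an entry rule based on possible relatedness. The reporters it names know allocation, and one of them sees only the active arm. Log counts therefore cannot support a between-arm statement about harm. The eating-disorder risk that the protocol screens out has no stated by-arm harm summary, although EDE-Q 6.0 and weight are scheduled alike in all arms.

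Two stronger readings should be resisted. A reader might infer that the log will show a false active-arm excess of a particular size. The document gives no detection rates, so the figures above are illustrations, and with a narrow gap the effect is small. A reader might also infer damage to the efficacy conclusions. The primary outcome is a survey score collected on one schedule in every arm and does not depend on the log.

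**What to change.** 1. **Statistical analysis plan section.** Report by arm at 3 and 6 months, descriptively and without alpha:
   - any EDE-Q 6.0 compensatory behaviour (vomiting, laxatives or diuretics, overexercise), and new onset among those with none on the baseline EDE-Q 6.0, each with exact 95% CIs;
   - between-arm differences in EDE-Q restraint and global score from the same linear mixed model, with 95% CIs;
   - BMI change from screening.
2. **Data management and monitoring.** Log adverse events regardless of judged relatedness and record relatedness as an attribute of each event. Reports to the ethics committee can stay limited to possibly related events. Recruitment closed in April 2022, so if the rule changes during the study, flag the date so that the two logging regimes can be told apart.
3. **Same section.** State that, because contact differs by arm, log counts will not be compared between arms. This is needed even with item 2, since logging all events does not remove unequal detection.

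The cost is one log column, a few more entries, a few tables, and registration of the amendment with the ethics committee and trial register. No new measurement or participant is needed. The estimates will be imprecise self-report: they describe harm and cannot exclude a modest excess.
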